
### 2.9. Statistical Analysis

#### 2.9.1. Primary Analyses

Each composite score (acceptability, trust, perceived risk) will be analyzed by a mixed repeated-measures ANOVA, with autonomy level (four scenarios) as the within-subjects factor and presentation sequence (four Williams sequences) as the between-subjects factor. The Greenhouse–Geisser correction will be applied when Mauchly’s test indicates a sphericity violation (Huynh–Feldt for ε between 0.75 and 1), and the multivariate approach (Pillai’s criterion) will be reported in parallel as a sphericity-robust check. H1 and H2 will be tested with within-subjects trend contrasts across the autonomy gradient. Because acceptance need not fall in a straight line, the complete set of orthogonal polynomial contrasts—linear, quadratic, and cubic—is pre-specified, and each is reported together with the proportion of the omnibus effect it accounts for. A purely linear profile leaves the quadratic and cubic components negligible, whereas a step between two adjacent levels appears as a large linear component accompanied by a substantial quadratic or cubic one. Because every monotone step is linear-dominant, the polynomial decomposition establishes departure from a straight line but cannot by itself locate the break; the break is identified only from the Holm-corrected adjacent-pair contrasts (A–B, B–C, C–D). A quadratic-dominant profile with a small linear component would instead indicate a non-monotone pattern, which the hypotheses do not predict and which would be reported as such. A non-monotonic or threshold pattern will be reported as such rather than summarized by the linear trend alone. Post hoc comparisons use dependent-samples *t*-tests for the six scenario pairs with Holm’s sequential correction, applied within each hypothesis-defined family of tests in line with current guidance on multiplicity control [74]. Effect sizes will be reported as partial η^2^ for omnibus tests and Cohen’s dz for pairwise comparisons, with 95% confidence intervals, following effect-size-centered reporting recommendations [64]. Assumption checks include graphical inspection of difference-score distributions; as a distributional robustness analysis, the Friedman test with Holm-corrected Wilcoxon signed-rank pairwise comparisons will be reported alongside each primary test—supplemented by ordinal (cumulative-link) models as sensitivity analyses for the Likert-based outcomes [71]—and the concordance of parametric and nonparametric conclusions stated explicitly. Order dependence is tested directly as the scenario × sequence interaction; a non-significant interaction, together with equivalence of the four sequence-specific profiles, supports pooling across sequences. Independently of that test, the autonomy effect is re-estimated from a linear mixed model with random intercepts per participant and additive fixed effects of autonomy level and serial position (1–4). The Williams square renders this model identified, so the estimate is adjusted for arbitrary—not merely linear—serial-position and fatigue effects, while first-order carry-over is balanced by the design rather than modeled; position-adjusted and unadjusted estimates are reported side by side, and any material divergence between them is treated as evidence of an order artifact and interpreted accordingly. Perceived difficulty (DIF1) and perceived technical sophistication (MAN2) are each added as time-varying covariates in further sensitivity models, addressing fatigue and the possibility that responses track the apparent complexity of the system rather than its autonomy. Finally, between-person heterogeneity in response profiles is examined by adding a random slope for the linear autonomy contrast and testing the improvement in fit by a likelihood-ratio test; a substantial random-slope variance indicates that an average trajectory conceals distinct response patterns and licenses the exploratory typology described in Section 2.9.2. Because a non-significant test is not evidence of absence, a smallest effect size of interest of *dz* = 0.20—the value detectable at the Bonferroni bound for the six pairwise contrasts at *N* = 300—is fixed in advance, and equivalence testing by two one-sided tests against that bound is reported alongside every null pairwise result, so that any claim that two adjacent scenarios do not differ rests on an equivalence test rather than on the absence of significance.

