## Abstract

Artificial intelligence (AI) is entering surgical planning along a continuum that runs from imaging assistance to near-autonomous plan generation, and facial reconstructive surgery—where outcomes bear directly on identity and social functioning—is among the most sensitive settings for this transition. Existing acceptability research has largely compared AI-supported care with conventional care in binary designs, and Central and Eastern European populations remain underrepresented. This protocol describes a cross-sectional, within-subjects vignette experiment among Romanian adults recruited online (target *N* = 300 valid responses; minimum analyzable *N* = 140, raised by a pre-registered rule if the pilot’s inter-scenario correlation falls below the planning assumption). Each participant will read four hypothetical scenarios describing progressively autonomous AI involvement in facial reconstructive surgical planning: imaging assistance, decision support, outcome simulation, and autonomous planning. Participants are randomly allocated to one of the four sequences of a Williams balanced Latin-square design, so that the autonomy level is orthogonal to serial position and to first-order carry-over. After each scenario, they will rate acceptability, trust, and perceived risk (three seven-point Likert items each), responsibility attribution across four loci (surgeon, hospital, AI developer, unavoidable medical uncertainty), perceived AI control and perceived technical sophistication (manipulation checks), and scenario difficulty. Primary analyses are mixed repeated-measures ANOVAs with presentation sequence as a between-subjects factor, orthogonal polynomial (linear, quadratic, cubic) trend contrasts, and Holm-corrected pairwise comparisons, complemented by a position-adjusted linear mixed model; secondary analyses address responsibility migration and concentration, moderation by AI familiarity, and global implementation preferences. A pilot study (*N* = 50, allocated 1:1 to the ascending and descending sequences) will establish reliability, factor structure, comprehension, manipulation validity, and a first bound on order effects before pre-registration on the Open Science Framework and the start of data collection.

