## 2. Materials and Methods

### 2.1. Study Design

This is a cross-sectional, vignette-based experiment with a four-level within-subjects (repeated-measures) design. Vignette experiments combine the internal validity of experimental manipulation with survey feasibility and are an established method for isolating drivers of health-related judgments [61]; their design and analysis follow current methodological guidance for vignette data [62]. Each participant reads and evaluates all four scenarios of AI implementation (A–D), presented in a counterbalanced sequence. The within-subjects structure makes each respondent their own control, eliminating inter-individual variability from between-scenario comparisons and substantially increasing statistical power relative to a between-subjects design of the same size [63]. The presentation sequence is counterbalanced. The survey platform allocates participants at random, in equal proportions and independently of any participant characteristic, to one of the four sequences of a Williams (balanced Latin-square) design: A → B → C → D, B → D → A → C, C → A → D → B, and D → C → B → A. In this square, every scenario occupies every serial position exactly once, and every ordered pair of scenarios occurs exactly once, so that autonomy level is orthogonal both to serial position and to first-order carry-over, and an additive model containing a four-level autonomy effect and a four-level serial-position effect is fully identified. The theoretically motivated ascending sequence and its exact mirror image are retained as two of the four arms. A fixed ascending presentation would have mirrored the progressive continuum under investigation and given every participant an identical evaluation context, but it would have left order, carry-over, and fatigue effects inseparable from the autonomy gradient; because H1–H3 concern precisely that gradient, internal validity was given priority over uniformity of context. Counterbalancing also makes the embedded manipulation check diagnostic rather than merely descriptive: perceived AI control should track the described autonomy level within every sequence, whereas an anchoring or fatigue artifact would instead track serial position—a distinction that a monotonic manipulation-check profile obtained under a fixed order cannot draw. Presentation sequence is therefore retained as a between-subjects factor in all primary models, a second manipulation check (perceived technical sophistication) separates autonomy from technical complexity, and a per-scenario difficulty item indexes fatigue (Section 2.6, Section 2.7, Section 2.8, and Section 2.9.1). The study involves no medical, pharmacological, or surgical intervention. Reporting of the completed study will follow current recommendations for effect-size-based reporting [64] and, for the web-survey component, the CHERRIES checklist as operationalized in recent methodological guidance [65]. Publication of the protocol in advance of data collection is intended to reduce publication bias and analytic flexibility [66,67].

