
The recruitment target is *N* = 300 valid participants. This target is dictated not by the within-subjects effects (for which power at *N* = 300 is 0.99 for small effects at ρ = 0.50, with a minimum detectable effect of *f* = 0.07), but by the person-level analyses: the familiarity moderation (minimum detectable interaction *f*^2^ = 0.037 at *N* = 300), the global preference test (minimum detectable *w* = 0.21 on 5 degrees of freedom), and descriptive analyses of demographic subgroups. A small interaction effect (*f*^2^ = 0.02) would require *N* ≈ 550; H4 therefore remains partially exploratory, and a non-significant result will not be interpreted as evidence of absence. At *N* = 300, dependent pairwise comparisons detect differences from *dz* = 0.16 (uncorrected) and *dz* = 0.20 (at the Bonferroni bound for six pairwise comparisons), so all six scenario contrasts can be treated as confirmatory. Counterbalancing entails no loss of sensitivity for the primary comparisons: with sequence entered as a four-level between-subjects factor, the autonomy main effect retains 3 degrees of freedom and the same noncentrality, so the minimum detectable effect at *N* = 300 remains *f* = 0.07. The scenario × sequence interaction—the direct test of order dependence—carries 9 degrees of freedom and a minimum detectable effect of *f* = 0.08 at ρ = 0.50 (*f* = 0.10 at ρ = 0.30), giving power of 0.95 against a small order effect of *f* = 0.10; the serial-position main effect in the additive model carries 3 degrees of freedom and matches the sensitivity of the autonomy effect itself. Order artifacts large enough to masquerade as the hypothesized autonomy gradient are therefore detectable, rather than being assumed away. In the pilot, by contrast, the ascending and descending arms (*n* = 25 each) bound order effects only at *f* = 0.17, which excludes medium-to-large artifacts but not small ones; the definitive test is the main-study interaction. Table 2 summarizes the power analysis, and Figure 1 shows achieved power as a function of the number of valid responses.

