
#### 2.9.2. Secondary and Exploratory Analyses

(i) Moderation (H4): the scenario × AI familiarity (B1, centered) interaction, via repeated-measures ANCOVA or a linear mixed model with random intercepts per participant, the recommended framework for vignette data [62]; presentation sequence is retained as a between-subjects factor here, as in every repeated-measures model in this protocol. (ii) Person-level multiple regression: mean acceptability across scenarios predicted by AI familiarity, general AI attitudes, and demographics (reporting *B*, *SE*, β, 95% CI, R^2^, VIF). (iii) Responsibility migration (H3): a 4 × 4 mixed ANOVA (scenario × actor, RES1–RES4, both within-subjects; presentation sequence between-subjects) with Greenhouse–Geisser correction; the scenario × actor interaction is the direct test of H3. Because H3 is confirmatory, it receives the same order controls as H1 and H2: the sequence terms are inspected first, and the migration estimate is repeated in a linear mixed model containing an additive serial-position term. (iv) Responsibility concentration: a normalized Herfindahl–Hirschman index computed per scenario from the relative weights of the three responsible actors (surgeon, hospital, AI developer; RES4—unavoidable medical uncertainty—is not a responsible actor and is analyzed separately), compared across scenarios by mixed repeated-measures ANOVA with sequence as a between-subjects factor; low values index diffusion of responsibility across actors, operationalizing the “problem of many hands” described in the responsibility literature [44,45]. (v) RES5 (moral duty) and RES6 (outcome-independent accountability): mixed repeated-measures ANOVAs across scenarios with sequence as a between-subjects factor, Holm-corrected within the family. (vi) Global preference (P1): a goodness-of-fit chi-square with standardized residuals over six analysis categories on 5 degrees of freedom. The six categories are the four scenarios, “I would prefer AI not to be involved in any way,” and a combined “no clear preference” category; the last pools the item’s two undecided options (“I have no preference” and “I cannot decide”), which are combined a priori because neither expresses a preference between scenarios and each is expected to be sparse. Consistency between stated preference and each participant’s maximum-acceptability scenario is reported descriptively. (vii) Exploratory: P4a and P4b (the surgeon’s permanent legal and, separately, moral responsibility) analyzed descriptively, compared with each other by a dependent-samples test on the within-person difference, and correlated with RES5/RES6; free-text concerns (P2) summarized by brief thematic analysis. (viii) Sensitivity analyses: primary analyses repeated (a) excluding participants with a single attention-check failure (who are retained under the primary rule) and (b) excluding participants with any comprehension failure, to demonstrate that conclusions do not depend on the cleaning criteria [69]. (ix) Order effects: descriptive profiles by sequence, the scenario × sequence interaction with its effect size and 95% confidence interval, and sequence-specific manipulation-check profiles. (x) Response-pattern typology (exploratory): where the random-slope test of Section 2.9.1 indicates heterogeneity, individual acceptability trajectories across autonomy levels are classified by latent-class growth analysis, with class enumeration by BIC and entropy and a minimum class size of 5% fixed in advance, and class membership described against AI familiarity, healthcare-system trust, and demographics; no inferential claim is attached to this analysis. (xi) Healthcare-system trust (B6) enters the person-level regression of (ii) as a covariate and is examined as an exploratory moderator of the autonomy effect, alongside healthcare contact frequency (B5) and prior surgical experience (B4, B4a). (xii) Subgroup analyses, all of which are secondary or exploratory, are governed by a minimum-cell rule fixed in advance: inferential tests within a subgroup are reported only where that subgroup contains at least 50 valid participants, the size at which a within-subject difference in *dz* = 0.40 is detectable at power 0.80; subgroups of 30–49 are reported descriptively with 95% confidence intervals and labeled as underpowered; subgroups below 30 are pooled into a residual category or not reported. A difference between subgroups is never inferred from a significant effect in one and a non-significant effect in another; only the formal interaction term, with its own confidence interval, supports such a claim. The set of moderators is fixed a priori, in the pre-registration, to seven: AI familiarity (B1), healthcare-system trust (B6), healthcare contact frequency (B5), prior surgical experience (B4/B4a), education (D3), age (D2), and field of activity (D4). Results are reported for all seven irrespective of significance, and no further moderator is added after the data are seen. (xiii) Missing data: because all closed items are mandatory, missingness in the dependent variables is structurally impossible within a submitted questionnaire. Two other forms of missingness remain. The first is unit-level, from questionnaires abandoned before submission. The platform is configured not to store partial submissions, so responses from abandoned questionnaires are neither retained nor analyzed (Section 2.10 and Appendix A.1). Attrition is therefore characterized from the platform’s page-level counters—how many participants reached each page—rather than from partial response data, and is reported as drop-out by serial position in the participant-flow diagram. Analyses are accordingly restricted to complete cases, that is, participants with all four scenario blocks, and no imputation is performed: with no partial records retained, there are no incomplete cases to impute. The second is item-level, on the background and demographic items that offer a “prefer not to answer” option or, in the case of B4 and B4a, are not displayed where the explicit health-data consent is declined; these are treated as a distinct category descriptively and as missing in inferential models, with a sensitivity analysis retaining the category in the person-level regression. Because complete-case analysis is not neutral when attrition is differential, drop-out is compared across the four presentation sequences, and any imbalance is reported and carried into the interpretation of the order analyses. All tests are two-tailed at α = 0.05, with exact *p*-values, effect sizes, and 95% confidence intervals reported for all tests, including non-significant ones. On closed 1–7 scales, no distribution-based outlier removal is applied.

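### The six confirmatory pairwise comparisons are specified as raw paired t-tests without sequence, although sequence is to be kept in all primary models; the equivalence tests state no sequence term either

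*Protocol article*

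**What the plan says.** Two statements commit the plan to sequence. Section 2.1: "Presentation sequence is therefore retained as a between-subjects factor in all primary models". Section 2.9.2(i): "presentation sequence is retained as a between-subjects factor here, as in every repeated-measures model in this protocol".

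The pairwise comparisons carry confirmatory weight. The Abstract lists them among the primary analyses: "Primary analyses are mixed repeated-measures ANOVAs with presentation sequence as a between-subjects factor, orthogonal polynomial (linear, quadratic, cubic) trend contrasts, and Holm-corrected pairwise comparisons". Section 2.5 says that the detectable differences are small enough, "so all six scenario contrasts can be treated as confirmatory". Section 2.9.1 rests the location of any threshold on them alone: "the break is identified only from the Holm-corrected adjacent-pair contrasts (A–B, B–C, C–D").

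The test itself is fixed in Section 2.9.1 and repeated in Table 5 for H1 and H2: "Post hoc comparisons use dependent-samples" t-"tests for the six scenario pairs with Holm’s sequential correction". Neither place gives a sequence or position term. Section 2.9.1 also sets equivalence tests against a bound of dz = 0.20, again with no sequence term and without saying which SD standardises dz.

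Order is controlled elsewhere. Section 2.9.1 tests the scenario × sequence interaction and fits a mixed model with additive serial position, where "position-adjusted and unadjusted estimates are reported side by side". Section 3 makes that model the primary basis for H1–H3 if an interaction appears.

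**The concern.** The design was counterbalanced so that the autonomy gradient could be separated from order. In a Williams square the distance in serial position between two scenarios changes with the sequence. A raw paired difference therefore absorbs any position effect. With equal sequences it enters as extra variance; with unequal completed sequences it also shifts the mean. The ANOVA with sequence removes the variance, and equal weighting of the sequences removes the shift. The paired t-test does neither.

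The affected tests are the ones meant to show where acceptance breaks. The equivalence tests share the problem: their bound is on the dz scale, so an inflated SD widens it in raw units. Section 2.9.2(xiii) restricts analysis to complete cases and concedes that differential attrition is not neutral, so unequal completed sequences are foreseen.

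**Working it through.** **Inputs from the protocol article.** N = 300, ρ = 0.50, two-sided α = 0.05 or 0.05/6, the dz values of 0.16 and 0.20 (Section 2.5, Table 2), and the four sequences (Section 2.1). **Assumed, because the article gives none:** a linear drift δ of 0.10 or 0.20 composite SD per position, and completed shares of 30/25/25/20.

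**1. The plan's own figures.** Noncentral t on paired differences, df = 299, power 0.80: minimum dz = 0.162 (α = 0.05) and 0.202 (α/6). Both stated values reproduce. Power at exactly dz = 0.20 and α/6 is 0.79. With sequence in the model (df = 296) the minimum dz is still 0.162 and 0.202.

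**2. Position gaps** (second scenario minus first), in sequence order ABCD, BDAC, CADB, DCBA:

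| Pair | Gaps | Mean | Mean square |
|---|---|---|---|
| A–B, C–D | +1, −2, +2, −1 | 0 | 2.5 |
| A–C, B–D | +2, +1, −1, −2 | 0 | 2.5 |
| B–C | +1, +3, −3, −1 | 0 | 5 |
| A–D | +3, −1, +1, −3 | 0 | 5 |

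All means are zero, so equal sequences give no bias from an additive position effect.

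**3. Variance.** With composite SD 1, the within-sequence variance of a difference is 2(1 − ρ) = 1. The raw variance is 1 + δ² × mean square:
- A–B and C–D: 1.025 (δ = 0.10) and 1.10 (δ = 0.20).
- B–C and A–D: 1.05 and 1.20.

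**4. Power at within-sequence dz = 0.20, α/6.** The raw dz becomes 0.20/√(raw variance):
- A–B and C–D: 0.78 and 0.74.
- B–C and A–D: 0.77 and 0.69.
- Sequence-adjusted: 0.79 throughout.

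Simulation with exactly 75 per sequence gives 0.71 rather than 0.69 in the worst cell, so about 0.70 is a fair summary. The raw test is conservative here: A–D type I error is 0.047 and 0.032 at nominal 0.05.

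**5. Unequal completed sequences (90/75/75/60).** Bias is δ × the weighted mean gap:
- A–D: 0.30×3 − 0.25 + 0.25 − 0.20×3 = 0.30, so 0.03 and 0.06 SD.
- A–B and C–D: 0.30 − 0.50 + 0.50 − 0.20 = 0.10, so 0.01 and 0.02 SD.
- B–C: 0.30 + 0.75 − 0.75 − 0.20 = 0.10, the same.

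Type I error for A–D, with these counts fixed:
- δ = 0.10: the shift is 0.03√300 = 0.52 against a cutoff of 1.968√1.049 = 2.016, giving about 0.07.
- δ = 0.20: the shift is 1.04 against 1.968√1.196 = 2.152, giving about 0.13.

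Both are slightly higher if the counts vary around these shares. In simulation the adjacent pairs stay at 0.04–0.05.

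**6. Equivalence tests.** If the raw SD standardises dz, the 0.20 bound becomes 0.20√1.20 = 0.219 composite SD for B–C and A–D at δ = 0.20. With the true within-sequence dz at the bound and equal sequences, false equivalence rises from 0.05 to 0.07.

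**7. Would the Section 3 switch be triggered?** An additive position effect lies wholly in the scenario × sequence interaction, with f = δ√1.25. At δ = 0.10, f = 0.112 and λ = 0.0125 × 300 × 4/0.5 = 30. On 9 and 888 df, power is 0.986. At δ = 0.20 it is about 1.00. At ρ = 0.30 the figures are 0.92 and about 1.00.

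**The case against.** The strongest reply is that the plan already answers this. Where the drift is large enough to matter, the interaction test would almost always detect it, and Section 3 then makes the position-adjusted estimate primary. At a drift of 0.05 SD per position, variance rises by at most 5 × 0.05² = 1.25%. Adjusted and unadjusted estimates are shown together in any case, allocation is equal, and balance is monitored (Section 2.7). A two-condition follow-up t-test might also not count as a primary or repeated-measures model.

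Much of this stands. A reader might infer that the plan ignores order, or that the located break will be biased. The documents support neither. Order is tested and modelled, equal sequences leave the raw differences unbiased, and the larger bias in the example falls on A–D, which does not locate the break. For C–D, where Section 3 expects the largest drop, the power loss is at most about 5 points in the range examined. Also, α/6 is only Holm's first step, so losses at later steps are smaller.

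One gap remains. Nothing links the Holm-corrected tests, dz or the equivalence tests to the adjusted model, even after the switch. The semantic defence is weak too, because the Abstract places these comparisons among the primary analyses and Section 2.5 calls them confirmatory.

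**Conclusion.** The point holds as an inconsistency with a modest consequence that is cheap to remove. The commitment on sequence and the specified pairwise tests do not agree, and these tests alone locate the break.

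Without a position effect nothing changes. With one and equal sequences, the cost is precision and a smaller dz: at most about 0.05 of power for A–B and C–D and about 0.09 for B–C and A–D, with equivalence slightly too easy to declare. With unequal completed sequences there is also bias, mainly in A–D. All these sizes rest on assumed linear drifts of 0.10–0.20 SD per position, ρ = 0.50 and, for the bias, the assumed 30/25/25/20 split.

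It would be wrong to conclude that the sample size is inadequate. No stated power, sample-size or dz figure is in error.

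**What to change.** - Take the six pairwise contrasts and the equivalence tests from the model containing sequence: the equal-weight average of the four sequence-specific differences, with pooled within-sequence error on N − 4 df. Apply Holm to those p-values.
- State that the within-sequence SD standardises both dz and the 0.20 equivalence bound.
- State that, when the Section 3 switch applies, the pairwise contrasts and equivalence tests come from the position-adjusted model.
- Align Section 2.9.1 and Table 5, and reconcile the post hoc label there with the confirmatory status in Section 2.5.

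The cost is 3 of 299 df, which leaves the minimum detectable dz at 0.16 and 0.20, and a dz defined on the within-sequence SD. With unequal sequences, equal weighting costs a little more: at 90/75/75/60 the variance factor is 300 × (1/90 + 2/75 + 1/60)/16 = 1.02. Section 2.12 states that pre-registration and data collection have not begun, so the change can be made now without counting as a deviation.
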